## Abstract

**Background:**

Decision Boxes are summaries of the most important benefits and harms of health interventions provided to clinicians before they meet the patient, to prepare them to help patients make informed and value-based decisions. Our objective is to explore the barriers and facilitators to using Decision Boxes in clinical practice, more precisely factors stemming from (1) the Decision Boxes themselves, (2) the primary healthcare team (PHT), and (3) the primary care practice environment.

**Methods/design:**

A two-phase mixed methods study will be conducted. Eight Decision Boxes relevant to primary care, and written in both English and in French, will be hosted on a website together with a tutorial to introduce the Decision Box. The Decision Boxes will be delivered as weekly emails over a span of eight weeks to clinicians of PHTs (family physicians, residents and nurses) in five primary care clinics located across two Canadian provinces. Using a web-questionnaire, clinicians will rate each Decision Box with the Information Assessment Method (cognitive impacts, relevance, usefulness, expected benefits) and with a questionnaire based on the Theory of Planned Behavior to study the determinants of clinicians’ intention to use what they learned from that Decision Box in their patient encounter (attitude, social norm, perceived behavioral control). Web-log data will be used to monitor clinicians’ access to the website. Following the 8-week intervention, we will conduct semi-structured group interviews with clinicians and individual interviews with clinic administrators to explore contextual factors influencing the use of the Decision Boxes. Data collected from questionnaires, focus groups and individual interviews will be combined to identify factors potentially influencing implementation of Decision Boxes in clinical practice by clinicians of PHTs.

**Conclusions:**

This project will allow tailoring of Decision Boxes and their delivery to overcome the specific barriers identified by clinicians of PHTs to improve the implementation of shared decision making in this setting.

## Background

Shared decision making (SDM) is an approach where healthcare professionals and patients make joint decisions based on the best evidence of the benefits and harms of all available options, and patients’ values and preferences in regard to those options
[1]. Patient Decision Aids are the tools most often used to facilitate SDM. They provide patients with information on the options and research-based outcomes relevant to health status, and help to clarify values regarding the benefits and harms of each option
[2]. They have been associated with favorable outcomes such as greater knowledge, lower decisional conflict, and lower proportion of people passive in decision making or undecided
[2]. Despite that Patient Decision Aids help them make informed decisions, many patients are still turning to their healthcare professional for recommendations. Clinician knowledge and recommendations are recognized as essential elements of SDM
[3], but clinicians often lack the tools to translate their knowledge to their patient and facilitate patients’ involvement in decision making.

To prepare healthcare professionals for SDM, we have involved both professionals and patients in the development of short clinical summaries, named ‘Decision Boxes’, that integrate the best available evidence from studies and knowledge syntheses to provide quantitative information on management options for medical questions that have no single best answer
[4,5]. The Decision Box is intended to help the clinician recognize that a decision needs to be shared with the patient, to prepare the clinician to communicate evidence-based information to the patient, and to assist the clinician in seeking patient’s values and preferences regarding the decision to be made.

Despite broad recognition of the merits of SDM, there is scarce evidence that health professionals put SDM approach into practice
[6-8]. The barriers to the implementation of SDM in clinical practice most often reported by health professionals are time pressure and the perception that SDM cannot be applied because of the patient’s characteristics or clinical situation
[9]. We developed Decision Boxes to try to address these barriers, for example by using a brief 2-page format, by offering prompts to initiate a discussion with the patient, and by providing first-hand evidence on decisions commonly encountered in primary care
[4]. However, we lack evidence on clinicians’ perceptions of the Decision Box, and on the best way to implement Decision Boxes within primary healthcare teams (PHTs).

### Objectives

Our objective is to study the barriers and facilitators influencing Primary Healthcare Teams’ uses of Decision Boxes in clinical practice. Our specific questions are: (1) What are clinicians' perceptions of the usefulness of the Decision Box? (2) Do clinicians intend to use information from Decisions Boxes in clinical practice? (3) What aspects of the primary care practice environment affect the use in practice of what clinicians learned from Decisions Boxes?

### Theoretical underpinnings

The proposed project is based on the theory of mechanisms of planned change as described in the Ottawa Model of Research Use (OMRU)
[10,11] (Figure
1).Derived from evidence and theories of change, the OMRU recognizes that practice change is not a linear process, but involves simultaneous and interactive relationships between the nature of the innovation, the potential adopters, and the context within the practice environment. Three key processes involved are: 1) assessing barriers and supports; 2) developing and monitoring interventions tailored to barriers and supports; 3) evaluating outcomes. The underlying mechanism is that tailoring intervention strategies to address barriers and strengthen facilitators related to the innovation (here Decision Box), potential adopters (here PHT) and practice environment (here primary care clinics) will result in practice change. Barriers and supports related to the innovation will be assessed with the Information Assessment Method
[12], those relative to potential adopters using Ajzen's Theory of Planned Behavior (TPB) (attitude, subjective norms, perceived behavioral control)
[13] and the Inter-Professional Shared Decision-Making (IP-SDM) model
[14,15], and those relative to the primary care practice environment using the IP-SDM model
[16]. We will use the identified barriers to tailor the Decision Box intervention before testing it in a future RCT. 

**Figure 1 F1:**
[figure not shown]
**Conceptual framework for the study of the implementation of Decision Boxes in primary healthcare teams (PHT), including factors explored and methods used.** Adapted from Graham and Logan
[10].

## Methods

### Study design

We will use a two-phase mixed methods study with an explanatory sequential design
[17], characterized by the collection and analysis of quantitative data in the first phase of research, followed by the collection and analysis of qualitative data in the second phase that builds on and explains the initial results of the quantitative component (Figure
2)
[17]. In the first phase, a previously validated questionnaire
[4] will be used to assess barriers and facilitators relative to the Decision Boxes as innovation. In the second phase, due to a lack of validated questionnaires, a qualitative study will be conducted to explain the barriers and facilitators relative to the environmental context. Quantitative and qualitative study findings will be interpreted together to adapt the Decision Boxes and the strategy to facilitate their use in clinical practice. 

**Figure 2 F2:**
[figure not shown]
**Proposed two-phase sequential explanatory study design.** In the first phase, quantitative (QUAN) data are collected via web questionnaires and analyzed to inform second phase. In the second phase, qualitative (QUAL) data are collected via interviews and analyzed. Both types of data are then interpreted together.

### Intervention

The intervention will consist of two elements: (1) eight evidence-based Decision Boxes written in both French and English on common primary care diagnostic, therapeutic and preventive interventions, and (2) a website hosting the Decision Boxes and a brief web-based tutorial to introduce the Decision Box. Each week, one of eight Decision Boxes (Table
1) will be delivered by email to the recruited clinicians for a total of eight weeks. Each email will also contain links to (1) the web-based tutorial, and (2) a web-based questionnaire for assessing each Decision Box.

**Table 1 T1:** Interventions covered by Decision Boxes

Screening	Box 1: 4. The serum integrated test to screen women for fetal trisomy 21
	Box 2: The BRCA1/2 gene mutation test to evaluate the risks of breast and ovarian cancer
	Box 3: The fecal occult blood test (FOBT) to screen for colorectal cancer
	Box 4: The prostate-specific antigen (PSA) test to screen men for prostate cancer
Prevention	Box 5: Acetylsalicylic acid (ASA) for primary prevention of cardiovascular disease
	Box 6: Bisphosphonates to prevent osteoporotic fractures in postmenopausal women
	Box 7: Statins for primary prevention of cardiovascular disease
Treatment	Box 8: Cholinesterase inhibitors to reduce the symptoms of Alzheimer’s disease

### Participants and recruitment strategies

 Five primary care clinics (such as FMU – Family Medicine Units - in Quebec and FHT- Family Health Team- in Ontario) will be recruited through professional networks of the members of the research team. They will include two French-speaking clinics and three English-speaking clinics. We will then invite all family physicians, nurses and residents working at those clinics to participate in the first phase of the study.

For phase two, a purposeful sample of eight clinicians per site, comprising 5 physicians, two nurses and one resident, will be randomly selected among extreme cases on the web-based questionnaires, i.e. clinicians who gave higher or lower scores to the Decision Boxes rated with the web-questionnaire. Thus, only the participants who completed at least one of the eight study questionnaires during phase one will be eligible to participate to phase 2. At each study site, we will also recruit a clinician with administrative responsibilities, such as the clinic Medical Director.

We will offer monetary compensation to the clinicians (CAN$100) who participated to the study interviews.

### Data collection and procedures

1. Phase one: quantitative study

At study entry, all participating clinicians will sign an informed consent form and complete a questionnaire assessing their demographic and professional characteristics (age, gender, number of years of clinical practice). They will also rate their interest for each of the eight Decision Box topics using a visual analogue scale ranging from "no interest" to "great interest". Then, clinicians will receive the eight Decision Boxes by email, at a rate of one per week for eight weeks. For each Decision Box received, they will be prompted to complete a web-based questionnaire (Additional file
1). The first part of this questionnaire consists of a 5-point smiley-faces rating scale to assess global satisfaction with that Decision Box. The second part consists of questions based on the Theory of Planned Behavior (TPB)
[13] to study the characteristics of the clinicians that influence their intention to perform a given behavior. In this case, the behavior under study was ‘to use what I learned from the Decision Box to precisely explain the advantages and disadvantages of the options to my next patient to whom this intervention might apply’. Based on the TPB, the three determinants of a clinician’s intention to perform a behavior are: his/her attitude toward performing this behavior (perceived advantages and disadvantages of performing a behavior), his/her subjective norm (normative beliefs about the social pressure to engage or not to engage in this behavior), and his/her perceived behavioral control (beliefs, based on experience, about one’s ability to adopt this behavior). The third part of the questionnaire comprises the Information Assessment Method (IAM) that serves to evaluate cognitive impacts of the information, its relevance, usefulness and expected benefits
[12].

2. Phase 2: qualitative study

At each site, we will conduct a 90-minute semi-structured interview with a mixed group comprising five family physicians, two nurses and one resident, and a 30-minute individual interview with a clinician with administrative responsibilities, such as the Medical Director of the clinic. These interviews will assess in-depth understanding of the implementation process and explore the influence of the practice environment on the clinical application of the knowledge which clinicians acquired from the Decision Boxes. Both the interview guides for individual and group interviews will be based on the conceptual model for IP-SDM
[14], and cover all key topics for all focus groups, although not necessarily in the same order (interviews will follow the natural progression of the conversation). This interview format will give participants the flexibility to explore emerging issues. All interviews will be moderated by the same interviewer (AG). One observer will take notes on the process and content of the discussions. Each discussion will be audiotaped and professionally transcribed.

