## Analysis plan and samples sizes

1. Phase one: quantitative study

We will first perform descriptive statistical analyses of the answers to the web-questionnaires. We will then use a mixed model to describe clinicians’ perceptions of the attributes of the decision boxes (5-point smiley-faces rating scale, IAM), taking into account the clinical topic of the Decision Box, the study site, clinician’s status (nurse, resident, physician) and socio demographic characteristics of the participants. We will also perform multiple regression analyses to test relationships between clinicians’ intention to use what they learned from the Decision Boxand the determinants of their intention (attitude, subjective norm, perceived behavioral control), their status (nurse, resident, physician), their sociodemographic characterisitics (age, gender, number of years in practice), the study site, and the clinical topic of the Decision Box.

The regression analysis between clinicians’ intention and its determinants was used to set the needed sample size of clinicians. Earlier studies estimated regression coefficients of 0.78 for physicians
[18], and of 0.63 for nurses
[19] between intention and the three determinants of the intention (attitude, behavioral control and subjective norm). To be conservative, we used the lowest regression coefficient obtained for nurses (R^2^ = 0.63) to calculate the sample size, using two potential confounding variables (clinical topics and clinicians’ status). The ‘clinic’ effect was considered negligible as we have previously measured an Intraclass correlation coefficient of only 0.02 for clinicians nested within clinics in a cluster randomized controlled trial
[20]. Using these parameters we evaluated that a sample size of 78 clinicians gave a power of 90%. Based on a study of a continuing medical education program in shared decision-making where 70% of the physicians attended at least two of the three workshops
[21], we expect that about 70% of participating clinicians will complete at least half of the eight online questionnaires (1 questionnaire/Decision Box; 8 Decision Boxes). Consequently, to achieve a sample size of at least 78 clinicians who will complete at least four questionnaires, we need to recruit 111 clinicians (n = 5 clinics; 22 clinicians/clinic).

2. Phase 2: qualitative study

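### Topic-specific baseline interest is collected but enters neither phase-one model, leaving within-topic differences in interest unadjusted in ratings and in response

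*Protocol article*

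**What the plan says.** Protocol article, Data collection and procedures, phase one: at entry clinicians "complete a questionnaire assessing their demographic and professional characteristics (age, gender, number of years of clinical practice"). The next sentence adds a separate measurement: "They will also rate their interest for each of the eight Decision Box topics using a visual analogue scale". This gives eight scores per clinician, all recorded before the first box is emailed.

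Protocol article, Analysis plan and samples sizes, phase one, sets out two models:

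- The mixed model for satisfaction and the Information Assessment Method is fitted "taking into account the clinical topic of the Decision Box, the study site, clinician’s status (nurse, resident, physician) and socio demographic characteristics of the participants".
- The multiple regression for intention uses the "determinants of their intention (attitude, subjective norm, perceived behavioral control), their status (nurse, resident, physician"), and sociodemographic characteristics spelled out, with the remaining terms, as ("age, gender, number of years in practice), the study site, and the clinical topic of the Decision Box".

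The sample-size paragraph allows for confounding "using two potential confounding variables (clinical topics and clinicians’ status"). On completion, it expects that "about 70% of participating clinicians will complete at least half of the eight online questionnaires".

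**The concern.** The interest score is the only baseline variable that is specific to both the clinician and the topic, and it is known whether or not the questionnaire for that topic comes back. The article names the covariates of both models and leaves this one out. It cannot be read into the sociodemographic set, which the same section defines as age, gender and years in practice.

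Two things are at stake.

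- **Selective response.** Clinicians can skip a week. If those with little interest in a topic skip it more often, the ratings for that box come from a more interested subset. A likelihood-based mixed model deals with missing ratings that depend on what is in the model, and interest is not in it.
- **Interpretation.** The Discussion presents the eight topics as an opportunity to study how clinical topic influences intention, and the results are meant to guide tailoring of the boxes. Within a topic, a low rating from an uninterested clinician and a low rating from an interested one point to different remedies. The planned models cannot tell them apart.

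**Working it through.** **1. Variables collected against variables modelled**

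| Variable at entry or in the questionnaire | Perception mixed model | Intention regression |
|---|---|---|
| Clinical topic, study site, status | yes | yes |
| Age, gender, years in practice | yes (as sociodemographics) | yes |
| Attitude, subjective norm, perceived behavioral control | no | yes |
| Interest in that box's topic | no | no |

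The topic term gives each topic its own mean. It therefore takes up differences in average interest between topics, but not differences between clinicians within a topic, nor selection on those differences.

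**2. How much non-response the plan expects**

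The plan's own figure is 78/0.70 = 111.4, against a stated recruitment of 111, so it reproduces to rounding (112 if rounded up). The 70% refers to clinicians who complete at least four of eight questionnaires. It bounds the average response per questionnaire without fixing it:

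- lowest: 0.70 × 4/8 + 0.30 × 0 = 35%
- highest: 0.70 × 8/8 + 0.30 × 3/8 = 81%

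The 50-70% used below lies inside these bounds but is an assumption.

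**3. Possible inflation of mean ratings**

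Assumptions, none of them in the documents: interest z is standard normal within a topic; the probability of answering is p(z) = 1/(1 + exp(−(a + g·z))), with a set to give the target response; the rating rises by b SD per SD of interest. Then

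- mean interest of respondents: m = E[z·p(z)] / E[p(z)]
- inflation of the respondents' mean rating = b × m

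| Response | g (log-odds per SD) | m (SD) | Inflation, b = 0.2 | Inflation, b = 0.5 |
|---|---|---|---|---|
| 50% | 0.5 | 0.24 | 0.05 | 0.12 |
| 50% | 1.0 | 0.41 | 0.08 | 0.21 |
| 60% | 0.5 | 0.19 | 0.04 | 0.09 |
| 60% | 1.0 | 0.33 | 0.07 | 0.17 |
| 70% | 0.5 | 0.14 | 0.03 | 0.07 |
| 70% | 1.0 | 0.25 | 0.05 | 0.13 |

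The range is about 0.03 to 0.2 SD. With g = 0 (response unrelated to interest) it is zero.

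**4. Intention regression**

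In a single-determinant approximation, leaving out interest shifts the standardized attitude coefficient by c × d, where c is the correlation of interest with attitude and d its direct effect on intention. With assumed c = 0.2-0.5 and d = 0.1-0.3, this is 0.2 × 0.1 = 0.02 to 0.5 × 0.3 = 0.15. If interest acts only through attitude, d = 0 and there is no bias.

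**5. Price of the extra term**

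Take 78 clinicians, a 3-df test of the determinants with 12 predictors in the model, alpha 0.05 (assumed), and an effect chosen to give 90.0% power. A thirteenth predictor lowers power to 89.97%. The targets of 78 and 111 are unaffected.

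**The case against.** **An article condenses.** A fuller plan may use the interest score, and collecting a variable without stating its use is common in a short analysis section. This lowers the weight of the point. It does not remove it, because the article lists the covariates of both models explicitly and interest is absent from both.

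**Theory supports leaving it out of the intention model.** Under the Theory of Planned Behavior, as the article describes it, attitude, norm and perceived control are the three determinants of intention. Prior interest may work largely through attitude, and adjusting for it could remove part of the relationship under study. This stands, and it is why that model should be shown both ways and not simply replaced.

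**The mixed model already helps.** Topic absorbs average interest. A clinician random effect, not stated but natural with repeated ratings, would recover some of a clinician's general enthusiasm from the other answers given. This stands in part: the figures in the working describe a plain respondent mean, and the bias left in such a model could be smaller. The clinician-by-topic part would remain.

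**Stronger readings that the documents do not support**

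- A reader might infer a precision gain, for instance by computing 78/(1 − r²), which is 86 at r = 0.3 and 104 at r = 0.5. That applies an assumed correlation with ratings to a sample size set for the intention regression. It would need r to be the partial correlation with intention after the three determinants and the other covariates, which may be near zero.
- A reader might infer that the interest score would let the study separate a good box from an interesting topic. Table 1 has one box per topic, so box and topic coincide at topic level whatever is added. Interest helps only within topic.
- A reader might infer that selective response on interest is established. The Discussion says that interest in Evidence-Based Medicine or shared decision making is likely to drive who joins, but it says nothing about who answers each week.

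**Conclusion.** The point holds as an inexpensive improvement to an exploratory, single-group study. The article collects topic-specific interest before exposure, gives it no stated use, and fixes two covariate lists that omit it. Within-topic variation in interest is therefore unadjusted in both models.

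The omission can be read directly from the text. The size cannot: about 0.03 to 0.2 SD of inflation in mean ratings depends wholly on the assumed response rate, response slope and rating slope, and its upper end needs the strongest values of all three. No comparison between arms and no decision threshold depends on these means, so the consequence is modest: ratings that may be somewhat optimistic, and topic contrasts and theory coefficients that may be partly confounded.

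**What to change.** 1. **Perception mixed model:** add the clinician's baseline interest score for that box's topic as a continuous covariate. Report adjusted means at the average interest of all recruited clinicians for that topic, respondents or not.
2. **Intention regression:** report the attitude, norm, control and topic coefficients with and without interest, and say in advance that overlap with attitude is expected.
3. **Response check:** for each box, compare baseline interest between clinicians who returned the questionnaire and those who did not.
4. **Interpretation:** state that, with one box per topic, interest helps separate appraisal of the box from interest only within topic.

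Cost: one extra term (1 df) and a second set of coefficients to report. The data are already to be collected, and the sample size does not change.
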